## **9 SAFETY**

### **9.1 Responsibility to Ensure the Safety of Trial Subjects**

The national regulatory authority, the sponsor (ISS), the institutions through which the research is performed and all members of the principal investigator's clinical team share responsibility for insuring that subjects in this trial are exposed to the least possible risk of adverse events that may result from participation in this protocol.

#### **9.1.1 Principal Investigator**

The Principal Investigator (PI) has a personal responsibility to closely monitor trial subjects and to ensure their safety. The principal investigator has the authority to request that the Sponsor convene the DSMB in the event of any safety concerns, and may delay an individual's study vaccine administration if the investigator has some suspicion that the study vaccine might place a subject at significant risk. The principal investigator or qualified designee determines severity and causality with respect to the investigational vaccine for each adverse event. As the study will be conducted on patients taking antiretroviral therapy, the management of subject safety should take into consideration the known adverse reactions caused by the drugs used in antiretroviral combination therapy, and should also explore the possibility of any "antiretroviral drug exchange" practiced by the subject. The principal investigator will be blinded for this study. In the event of an emergency where knowledge of the treatment allocation is required for proper clinical management of the subject, the principal investigator may require the un-blinding of the treatment assignment (active treatment or placebo). If possible, sponsor approval should be sought prior to any emergency un-blinding procedure (See Section 6.5).

##### **9.1.1.1 Study Vaccine Pausing Rules for the Principal Investigator**

In the event of a safety concern, the principal investigator has the authority to request that the Sponsor convene an ad hoc review of the safety data by the DSMB. Based on this review, the DSMB may choose to pause further vaccine administration in the study. (See Section 10.)

#### **9.1.2 Study Sponsor**

The Sponsor has an institutional responsibility to ensure subject safety. This responsibility is vested in a Data Safety Monitoring Board.

##### **9.1.2.1 Local Medical Monitor (LMM)**

The LMM is the sponsor's representative and is a registered medical practitioner in his/her country of residence with experience in HIV/AIDS related research and HAART treatment. The LMM will regularly review all safety data while being cognizant of the known adverse reactions caused by drugs used in antiretroviral combination therapy. The LMM may assist the Principal Investigator in the assessment of severity and causality for adverse events, and help the PI in exploring the possibility of any "antiretroviral drug exchange" that may have been practiced by the subject. In addition to the ongoing review of adverse events, the LMM, by virtue of his/her location will be immediately available to discuss the significance and possible impact of a SUSAR/SAE with the principal investigator. The LMM, like the principal investigator, will be blinded.

##### **9.1.2.1.1 Study Vaccine Pausing Rules for the Local Medical Monitor**

In the event of a safety concern the Local Medical Monitor in collaboration with the Principal Investigator will request that the Sponsor convene an ad hoc review of the relevant safety data

by the DSMB. Based on this review, the DSMB may choose to pause further vaccine administration in the study (See Section 10.)

### **9.1.3 Data Safety Monitoring Board (DSMB)**

The Sponsor will provide for the constitution of the Data Safety Monitoring Board for the monitoring of subjects' safety. The DSMB is composed of medical specialists with experience in HIV/AIDS-related clinical research and evaluation of investigational product safety issues. The primary responsibility of the DSMB is to protect the safety of subjects enrolled in the trial, by regular review of all safety data to verify no adverse changes to the pre-study risk-benefit ratio. The members cannot be directly involved with the conduct of the study. Additional subject area experts may be present to provide expertise if requested by the DSMB. According to their requirements the DSMB may review an individual SAE, or it may choose to review adverse events, serious adverse events, solicited adverse events, and laboratory and vital signs data. The DSMB may un-blind any amount of safety information needed to conduct their assessment. All procedures associated with this review, including objectives, data handling, and elements to be included for review will be documented in the DSMB minutes.

Based on its review of the safety data, the DSMB will make recommendations in the DSMB minutes to ISS regarding further conduct of the study and further administration of study treatment. The conclusions of the DSMB will be communicated to the Sponsor, Principal Investigator, Local Medical Monitor, Ethics Committees and the national regulatory authority for their concurrence. The Sponsor agrees to abide by the decision of its DSMB with concurrence of the national regulatory authority and the Ethics Committee.

## **9.2 Safety Surveillance during the Study**

Subjects will be monitored and safety data collected by way of clinical interviews, examinations, and evaluations of daily diaries conducted by study team members and through reports of laboratory evaluations.

### **9.2.1 Adverse Event (AE)**

An adverse event (AE) is defined as any unanticipated problem involving risks to study participants or others. An adverse event, therefore, can be any unfavorable or unintended sign, symptom, disease, syndrome, abnormal laboratory finding, or concurrent illness that emerges or worsens relative to the subject's pre-treatment baseline, whether or not it is considered to be related to the medicinal product.

All conditions that exist prior to administration of the study vaccine (pre-existing conditions) will be recorded in the subject's medical history to establish baseline. Day-to-day fluctuations in pre-existing conditions that do not represent a clinically significant change in the subject's status will not necessarily be reported as adverse events.

Any adverse change from the subject's baseline condition (determined from screening evaluations conducted to confirm study eligibility) that occurs following the administration of the study vaccine will be considered an adverse event. This includes the occurrence of a new adverse event or the worsening of a baseline condition, whether or not considered related to the study vaccine. Intermittent conditions such as headaches may be present on Study Day 0 but may represent an adverse event if the intensity or duration of the event is worse than usual following receipt of study vaccine. Adverse events include but are not limited to:

adverse changes from baseline that represent increases in toxicity grade according to the Toxicity Table, adverse changes in the general condition of the subject, signs and symptoms noted by the subject, concomitant disease with onset or increased severity after study vaccine administration, and clinically significant changes in laboratory safety parameters occurring after study vaccine administration.

The reporting period for all adverse events is the entire study period of 48 weeks. Adverse events will be reported on the Adverse Event CRF using a recognized medical term or diagnosis that accurately reflects the event. Adverse event evaluations will be reviewed by the principal investigator or by a designated medically qualified practitioner. Adverse event CRF pages are to be completed by members of the study team designated in writing by the principal investigator. The onset and resolution dates of the event and action taken in response to the event will be documented.

All adverse events must be followed until resolved or stabilized. The resolution date will be recorded on the CRF as the last date on which the subject experienced the adverse event or, if unresolved by the last day of the reporting period, the resolution date will be recorded on the CRF as “ongoing.” Information recorded on the CRF must be substantiated in the source documents. If an adverse event evolves into a condition that becomes “serious,” it will be designated as serious on the Adverse Event CRF and a SAE Report (SAER) form will be completed.

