### DAY 0 (Baseline)

#### Prior to the vaccine administration:

- Physical examination including weight;
- Vital signs after 5 minutes in a resting position (seated blood pressure, heart rate, respiratory rate and axillary body temperature)
- Concomitant medication
- Standard haematology, clinical chemistry, coagulation and urinalysis assessments (as described in section 6.6.2)
- Urine dipstick pregnancy test (for females of child-bearing potential only)
- CD4+ T cell counts
- HIV-1 plasma viraemia
- Anti-Tat antibodies (IgM, IgG, IgA)
- Cervical swab and Pap smear for detection of HPV infection (Female participants only)
- Review of medical history and eligibility criteria (before the first vaccination)
- Immunological & Virological sample collection and storage.

Note: If the subject has a body temperature  $\geq 37.5$  °C or, in the investigator's opinion, an acute illness, **DO NOT VACCINATE**; re-schedule the Day 0 visit.

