#### **9.4 Adverse Event Treatment, Follow-up and Outcome**

Treatment of any adverse events will be determined by the investigator using his/her best medical judgment and according to current clinical practice guidelines. All applied measures as well as follow-up will be recorded in the appropriate CRF. Adverse events will be considered resolved when the condition returns to normal or returns to the subject's baseline status as established on Study Day 0, or when the condition has stabilized with the expectation that it will remain chronic. Since the principal investigator will be blinded for this study, in the event of an emergency where knowledge of the treatment allocation is required for proper clinical management of the subject, the principal investigator may require the un-blinding of the treatment assignment (active treatment or placebo). If possible, sponsor approval should be sought prior to any emergency un-blinding procedure.

The investigator will continue follow-up on adverse events, including clinically significant laboratory abnormalities until the event has resolved, is otherwise satisfactorily explained, or the subject completes the study. If not reported earlier, the outcome of adverse events will be determined when the subject completes the study.

Follow-up for serious adverse events must continue until resolution and the outcome reported to ISS, even if this extends beyond the serious adverse event reporting period (i.e., after the final study visit). For analysis purposes, the outcome for serious adverse events will be determined on the final study visit.

If at any time after completion of the serious adverse event reporting period (the final study visit) the investigator becomes aware of a serious adverse event that is suspected by the investigator to be related to the study vaccine, the event must be reported to ISS.

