### 12.7 Secondary Endpoint Analysis

Changes from baseline in physical examination results, vital signs data and laboratory parameters will be summarized for both treatment groups.

MedDRA dictionary will be used for coding adverse events. Adverse events will be summarized by system organ class, preferred term, severity and relationship with the

vaccination; the incidence of adverse events “possibly”, “probably” or “certainly” related to vaccination will be computed. All serious adverse events (SAEs) will be summarized by treatment group, subject, gender, age, duration of the event, action taken, investigator’s assessment of causality and outcome.

Change from baseline will be summarized for CD4+ T cells and HIV viral load. Haematology, clinical chemistry and urinalysis results will be graded according to Appendix I and will be presented for both treatment groups.

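### Adverse events are opened against a screening baseline but closed against Day 0, so a relapse after vaccination to no worse than the screening level is not flagged by the defined baseline

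*Protocol*

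**What the plan says.** Protocol 9.2.1 describes baseline in three ways:

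- The general definition speaks of something that "emerges or worsens relative to the subject's pre-treatment baseline", naming no visit.
- The next paragraph states: "All conditions that exist prior to administration of the study vaccine (pre-existing conditions) will be recorded in the subject's medical history to establish baseline". That runs up to the first injection.
- The operative sentence then ties baseline to screening, "determined from screening evaluations conducted to confirm study eligibility", and limits events to an adverse change "that occurs following the administration of the study vaccine will be considered an adverse event".

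The same section lists, among its examples of events, "adverse changes from baseline that represent increases in toxicity grade according to the Toxicity Table". That item has no timing words of its own.

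Section 9.4 closes an event when the condition is normal, when it is back at "baseline status as established on Study Day 0", or when it has stabilised and is expected to stay chronic. Section 6.7 runs screening from Day -35 to Day -1. It labels the Day 0 visit as Baseline and repeats the examination, vital signs and haematology, chemistry, coagulation and urinalysis tests before the first vaccination. Medical history is reviewed at the same visit.

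**The concern.** One event can be opened against one reference point and closed against another, with the two up to 35 days apart. If status shifts in that interval, the two rules can disagree about the same finding. Adverse events are part of the secondary safety endpoint in 8.2 and are compared between arms.

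The opening rule matters more than the closing rule, because site staff apply it when deciding what goes on the adverse event form. Laboratory shifts can be recomputed later from stored values. A symptom or examination finding that was never recorded as an event cannot be recovered in the same way.

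**Working it through.** The protocol states no figure for this point, so there is nothing to reproduce. The check compares the two baselines on every possible pattern of toxicity grade.

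**Inputs**
- Opening baseline: screening, Day -35 to -1 (9.2.1, 6.7).
- Closing baseline: Day 0 before vaccination (9.4, 6.7).
- Grades: the toxicity table in Appendix I has grades 1 to 4. Adding 0 for no abnormality gives five levels.

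**Notation.** Let s, d and p be the grade at screening, on Day 0 and after vaccination. There are 5 × 5 × 5 = 125 patterns. An event opens against screening if p > s, and against Day 0 if p > d.

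**Results**
- p > s: 10 ordered pairs × 5 values of d = 50 patterns.
- p > d: likewise 50 patterns.
- s < p ≤ d (opens against screening but is no worse than Day 0, so it already meets the 9.4 return-to-baseline criterion): 10 with s < p < d plus 10 with p = d, total 20.
- d < p ≤ s (worse than Day 0 but not worse than screening, so the screening baseline does not flag it): 10 with d < p < s plus 10 with p = s, total 20.

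**Applying the timing clause.** Section 9.2.1 also requires the change to follow vaccination, so p > d must hold as well. Patterns with p > s and p > d number 0 + 1 + 4 + 9 + 16 = 30, which equals 50 − 20. The first group of 20 drops out. The second group of 20 is unaffected, because those patterns never exceeded screening.

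**With a single Day 0 baseline**, both mismatch groups fall to 0.

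These are counts of logical patterns, not expected frequencies. Many of the 125 would be rare in subjects who passed the eligibility criteria.

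**Example of what remains.** A subject has grade 1 at screening, 0 on Day 0 and 1 at Day 7. Against Day 0 the grade has risen by one. Against screening it has not risen, and the grade-increase item is silent.

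**The case against.** The strongest reply is that the rest of 9.2.1 does most of the work.

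A reader might infer that a value which worsened between screening and Day 0 and then stayed put becomes an adverse event. The text does not support that: such a value did not change after vaccination, and 9.2.1 treats conditions already present before vaccination as pre-existing. This part of the reply stands. The only residue is that the grade-increase item, read alone and applied mechanically against screening, could still lead someone to record the finding.

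The reply also reduces the remaining defect. The list of events in 9.2.1 is not exhaustive. It includes clinically significant laboratory changes, disease with onset or worsening after vaccination, and symptoms the subject notices, none of them tied to screening. Section 9.3 separately asks for clinically significant changes at any assessment to be recorded as events. Graded laboratory results are summarised by arm under 12.7 whether or not they were logged as events. All of this narrows the gap. It does not close it, because capture then depends on a judgement of clinical significance or new onset, and the one baseline that is tied to a visit points the other way.

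Two further points stand. Return to Day 0 status is only one of three routes to resolution in 9.4. Section 12.7 names no baseline visit for its change-from-baseline summaries, but that can be left to the statistical analysis plan, which is not shown, so it is not counted here.

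**Conclusion.** The inconsistency is real and lies in current text: 9.2.1 names screening, while 9.4 and 6.7 name Day 0, and 9.2.1 also disagrees with itself. Its practical consequence is narrow. A finding that improved by Day 0 and relapsed after vaccination to no worse than its screening level is not an adverse change or grade increase under the stated baseline, and is recorded only if judged clinically significant or a new onset.

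The size cannot be computed, because the protocol gives no rate of change between screening and Day 0. A reader might assume that 5–15% of subjects shift a grade in that interval and conclude that 10–30 of 200 are misclassified (0.05 × 200 and 0.15 × 200). That does not follow. A shift before Day 0 misclassifies nobody by itself; the post-vaccination value must also fall between the two baselines. A subject graded 0, 1, 0 opens no event under either rule.

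A reader might also infer that the rule tilts the safety comparison in the vaccine's favour. Under-recording in both arms could shrink a true difference. However, the false events that would add to such dilution are largely excluded by the timing clause, and what is left is unquantified. The effect is probably small, applies to both blinded arms, and leaves the primary endpoint and the sample size untouched. Correcting it is worthwhile because it improves event capture at almost no cost.

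**What to change.** In 9.2.1, replace the parenthesis that ties baseline to screening with the last value or status before the first vaccination on Day 0. Allow the screening value only where no Day 0 value exists; T4 and TSH, for example, are scheduled only at screening in Appendix II. State that this one baseline governs onset, toxicity-grade increase and resolution, so that 9.2.1 and 9.4 agree. Recording conditions that arise between screening and Day 0 as medical history is already the rule in 9.2.1 and needs no change.

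The cost is a wording change in one section, submitted as an amendment under 13.2, and a short note to site staff. The Day 0 pre-vaccination assessments are already scheduled, so no new visits, samples or data are required.

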### **9.2.2 Serious Adverse Event (SAE)**

Seriousness refers to the outcome of an adverse event. Seriousness is determined by the principal investigator (or qualified designee). If any of the following outcomes are present then the adverse event is serious:

- Results in death
- Is life-threatening (defined as an event in which the subject or patient was at risk of death at the time of the event; it does not refer to an event which hypothetically might have caused death if it were more severe)
- Requires inpatient hospitalization or prolongation of existing hospitalization
- Results in persistent or significant disability/incapacity
- Is a congenital anomaly/birth defect
- Is an important medical event [defined as a medical event that may not be immediately life-threatening or result in death or hospitalization but, based upon appropriate medical and scientific judgment, may jeopardize the patient/subject or may require intervention (e.g. medical, surgical) to prevent one of the other serious outcomes listed in the definition above]. Examples of such events include, but are not limited to, intensive treatment in an emergency room or at home for allergic bronchospasm, blood dyscrasias or convulsions that do not result in hospitalization.

A **serious adverse event** is an adverse event meeting the outcome criteria for seriousness regardless of relationship to an administered medicinal product.

### **9.2.3 Adverse Drug Reaction (ADR)**

An ADR is any untoward and unintended response to any dose of an investigational medicinal product administered in a clinical trial when the Principal Investigator (or qualified

designee) has judged that there is at least a reasonable possibility that the event was related to the product.

#### **9.2.4 Serious Adverse Drug Reaction (SADR)**

*A SADR is a SAE suspected to be causally related to the investigational product; a SUSAR is a Serious Unexpected Suspected Adverse Drug Reaction or unexpected SADR.*

### **9.3 Reporting of Adverse Events/Adverse Drug Reactions**

The identification and reporting of AEs/ADRs is the Investigator's responsibility. The collection of AE/ADR information will begin as soon as the study starts (when the first subject is enrolled).

AEs/ADRs may be either spontaneously reported or elicited during questioning and examination of a subject. All identified AEs/ADRs must be recorded and described on the appropriate page of the CRF in occasion of each visit scheduled within the clinical trial. If known, the diagnosis of the underlying illness or disorder should be recorded, rather than its individual symptoms.

Any clinically significant changes noted during interim or final physical examinations, electrocardiograms, haematological-biochemical-coagulation analysis, urinalysis and any other potential safety assessments, whether or not these procedures are required by the protocol, should also be recorded on the appropriate AE page of the CRF.

#### **9.3.1 Assessing Severity**

The safety concepts of "severity" and "seriousness" are distinct concepts. Severity refers to the degree of clinical manifestation. "Seriousness" refers to pre-defined outcomes from an adverse event. A severe adverse event is not always serious and a serious adverse event is not always severe.

For all adverse events the investigator (or qualified designee) is responsible for assessing the severity of the event and the causal relationship of the event to the study vaccine.

The severity of all adverse events, including clinical findings and abnormal laboratory values, will be classified as one of the following grades:

1. Mild
2. Moderate
3. Severe

A Toxicity Table (adapted for this protocol from the Division of Aids table for grading the severity of Adult and Pediatric Adverse Events Version 1.0, December, 2004; clarification August 2009) is provided as an appendix to the protocol for the assessment of severity of specified adverse events. The Toxicity Table Adverse Event Grades do not correlate directly with the classical severity grades of mild, moderate and severe. **For the purposes of recording events in the CRF** Toxicity Table Grade 1 events will be considered mild in severity, Toxicity Table Grade 2 & 3 events will be considered moderate in severity, and Toxicity Table Grade 4 events will be considered as severe.

For adverse events not listed in the Toxicity Table determination of severity requires some level of interpretation as outlined below. The degree of incapacity caused by the adverse event and the level of medical intervention required for treatment may be helpful in assessing the overall severity of the adverse event.

For example:

- Mild events are generally regarded as noticeable but have no impact on normal activities; they may or may not require over-the-counter treatment managed by the subject.
- Moderate events generally have some impact on an individual's normal activities and may require general symptomatic medical intervention by a healthcare professional or by the subject.
- Severe adverse events may be incapacitating, leading to suspension of normal daily activities, and would generally require more immediate medical evaluation and intervention by a healthcare professional.

A change in severity of an adverse event will not be recorded as a new adverse event. Only the highest severity level that occurs during the entire period of the adverse event will be recorded on the CRF with the onset and resolution dates encompassing the entire duration of the event.

